### Questionnaire data

At the three points (T0–T2), the pregnant women with periodontitis diagnosis answer questionnaires about sleep [36], physical activity level [37], frequency of food consumption [38], smoking habits, alcohol consumption, maternal conditions (general questionnaire), pregnancy complications, sunlight exposure, mental health [39], health general [40] and social support [41]. At the baseline, women also provided socioeconomic information. A specific questionnaire on Oral Health Impact Profile (OHIP) [42] was administered at baseline (T0) and 6–8 weeks postpartum (T2) (Fig. 1).

### Biomarkers and measures

Anthropometric (height and weight) and blood pressure are measured in T0–T2. Maternal blood samples were collected in the morning after 12-h overnight fast in the T0, T1 and after delivery (T2) for analysis of biochemical markers. Also 24-h urine is collected at three-time points (T0–T2) for analysis of urinary calcium and creatinine. Prior to the urine collection, all participants are carefully instructed regarding the specific procedures. The blood and urine samples are stored in a freezer with a temperature of − 80 °C until analysis in the Institute of Nutrition Josué de Castro at the Federal University of Rio de Janeiro.

### Recruitment period and setting

The participant recruitment period started in April 2017 and ended in May 2018 with follow-up scheduled until February 2019. The study is conducted in the Municipal Health Centre of Duque de Caxias, Rio de Janeiro/Brazil. This public health centre offers prenatal care for low-risk pregnant women, child health programmes, as well as a clinical laboratory. The population assisted by this centre is of low income and most of them live in the surrounding slums.

Duque de Caxias is a city in the metropolitan region located geographically in the Rio de Janeiro state with approximately 900,000 inhabitants [43]. Duque de Caxias presents a neonatal mortality rate of 12.1 per 1000 live births, 0.7% of maternal deaths investigated and 20.4% of families covered by the family health strategy [44]. These programmes are targeted at families that live under adverse conditions and whose nutritional status is impacted by multiple constraints such as living with some degree of food insecurity (limited access to adequate quantity and quality of food) [45].

The latitude of Duque de Caxias is 22^o^ 47′ S. This area of Brazil is usually sunny all year round. The climate is tropical and summers are hot and humid, while the winters are mild and with more restricted rainfall. The pollution index in this city is high according to the recommendations of the World Health Organization (mean annual concentrations of inhalable particles of diameter less than 10 μm < 20 μg/m^3^ [46], with a mean estimate of 45.9 (SD 21.6) μg/m^3^ between the years 2000–2008 [47].

### Participants and eligibility criteria

The study population includes low-risk adult pregnant women, with periodontitis, attending the prenatal care in the Municipal Health Centre of Duque de Caxias, Rio de Janeiro/Brazil. Inclusion and exclusion criteria are described in Table 2.

**Table 2 Tab2:** Inclusion and exclusion criteria for the IMPROVE feasibility trial

Inclusion criteria	Exclusion criteria
1. Aged ≥ 18 years at the time of recruitment	1. Positive diagnosis of HIV/AIDS, syphilis, psychosis, diabetes before pregnancy, thyroid disease, or any disorder causing vitamin D hypersensitivity (e.g. sarcoidosis and other lymphomatous disorders)
2. > 20 weeks gestation at first prenatal visit	2. Lactose intolerance, milk allergy, history of renal stones or family history of renal stone and hyperparathyroidism
3. Positive diagnosis of periodontitis (≥ 1 tooth with at least one site with ≥ 4 mm of clinical attachment loss (CAL) and presence of bleeding on probing)	3. Extensive dental cavity (crowns of several teeth destroyed by caries) and loss of tooth structure or use of fixed dental braces
4. Cognitively and physically able to complete an interview and oral examination and willing to participate, including provision of blood samples.	4. Use of antibiotics or any immune-suppressants or medication known to affect vitamin D/calcium metabolism
	5. Consumption of ≥ 4 servings/day of dairy products or taking vitamin D supplements > 400 IU/day

### Recruitment

In the first prenatal visit a member of the research team introduced pregnant women to the study and invited those initially interested in taking part to answer a preliminary checklist for eligibility, except for the diagnostic of periodontitis. After this, women were screened for syphilis and HIV, as part of the routine pre-natal care. Those who were preliminarily eligible and tested negative for syphilis and HIV were then invited to book a dental examination. Those who screened positive for periodontitis were provided with an informed consent form and included in the study (Fig. 2).

**Fig. 2 Fig2:**
[figure not shown]
Recruitment of participants *Pregnant women with periodontitis but presenting extensive caries were excluded

### Randomisation, allocation concealment and blinding

To avoid information bias, regarding influence of interviewer by knowledge of group allocation of participants, randomisation took place after baseline assessment. An online randomisation system with a random mixture of permuted block sizes, stratifying participants by current smoking habit (yes vs. no) was provided and concealed by *Sealed Envelope Ltdtm*.

Due to the nature of the intervention (early vs. late PT), complete blinding of the intervention was not possible. However, dentists and participants were blinded to group allocation regarding milk fortification. Outcome assessment is blinded, and the dentist performing the final periodontal examination is not aware of group allocation regarding both placebo or fortified sachet and PT before or after delivery.

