### Sample size

This is a feasibility study, and thus the final sample size will be determined by the number of participants that are feasible to recruit within the timescale and budget of the project. For feasibility studies, a minimum of 12 subjects per group is proposed by Julious [54], and a total sample size of 70 subjects is proposed by Teare et al. [55] for a continuous outcome. Since we are planning a 2 × 2 factorial RCT, a sample size of 120 (30 per group), would be enough to detect a realistic event and allowing for 58% dropout rates (considering a sample size of 70), with sufficient precision and minimal bias for the estimates, as well as the existence of an additive interaction between the two interventions.

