### Statistical analysis

Baseline characteristics of participants will be summarised using descriptive statistics (i.e. means and standard deviations for normally distributed continuous variables, medians and ranges for skewed continuous variables, frequencies and proportions for categorical/binary variables), for all four intervention arms and total sample. All analyses will be according to the intention-to-treat approach, including all participants, regardless of adherence to the study protocol. To determine the effects of the intervention, time and group-time interaction on outcomes (inflammatory biomarker concentrations and periodontitis status), one-way repeated measures ANOVA will be used. Intervention will be regarded as a between-subject factor and time with three-time points (T0, T1 and T2) as a within-subject factor. Mean change of biomarker concentrations, number of sites with bleeding on probing and clinical attachment level (periodontal status) will be compared between the four treatment groups using ANCOVA, adjusted for their baseline values. A *P* value < 0.05 will be considered statiscally significant.

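### Allocation is stratified by current smoking but the stated models leave smoking out, so ANCOVA standard errors are slightly too wide if smoking is prognostic beyond baseline

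*Protocol article*

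**What the plan says.** The section on randomisation, allocation concealment and blinding describes an online system using "a random mixture of permuted block sizes", "stratifying participants by current smoking habit (yes vs. no"). Smoking is the only stratification factor named, and no reason for choosing it is given.

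The Statistical analysis section sets out two models for biomarkers and periodontal status:

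- **ANCOVA.** Mean changes "will be compared between the four treatment groups using ANCOVA, adjusted for their baseline values".
- **Repeated measures.** For intervention, time and their interaction, "one-way repeated measures ANOVA will be used". Its factors are stated: "Intervention will be regarded as a between-subject factor and time with three-time points (T0, T1 and T2) as a within-subject factor".

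Smoking enters neither model. The significance rule is a P "value < 0.05 will be considered statiscally significant", and the Sample size section plans "a sample size of 120 (30 per group"). Table 1 lists the initial effects on biomarkers and periodontitis as secondary objective 6. Secondary objective 1 is to obtain effect sizes and variability for sizing the definitive trial.

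**The concern.** Blocking within smoking strata makes the arms nearly alike in their share of smokers. Differences between smokers and non-smokers then contribute little to the real sampling variation of an arm comparison. A model without smoking still counts those differences as residual error. If smoking is prognostic given the baseline value, the printed standard error exceeds the real one and the test rejects too rarely.

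Two things are at stake. One is some precision in a trial with 30 women per arm. The other is the residual SD, which is a stated product of this trial. If the definitive trial stratifies by smoking and adjusts for it, an SD from a model without smoking overstates what that trial needs.

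**Working it through.** The article gives no figure on this point, so there is none to reproduce.

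**Inputs from the article.** Two smoking strata; permuted blocks of mixed, unstated size; four equal arms, N = 120; ANCOVA on change with the baseline value as covariate; alpha 0.05.

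**Assumptions.** Smoking prevalence p = 5-30%. Smoking effect d, given the baseline value and in residual SDs, from 0 to 1. Two-sided testing.

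**Formula.** Let the residual variance with smoking in the model be 1. With arms balanced on smoking, the true variance of an arm contrast is based on 1. The model without smoking estimates 1 + p(1-p)d². So

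model SE / true SE ≈ √(1 + p(1-p)d²).

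At p = 0.30 and d = 0.5: √(1 + 0.21 × 0.25) = √1.0525 = 1.026. At p = 0.30 and d = 1: √1.21 = 1.100.

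| SE overstatement | d = 0 | d = 0.3 | d = 0.5 | d = 1 |
|---|---|---|---|---|
| p = 0.05 | 0% | 0.2% | 0.6% | 2.3% |
| p = 0.10 | 0% | 0.4% | 1.1% | 4.4% |
| p = 0.20 | 0% | 0.7% | 2.0% | 7.7% |
| p = 0.30 | 0% | 0.9% | 2.6% | 10.0% |

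**Simulation of the ANCOVA.** Each setting had 3,000 trials with stratified blocks of 4 and 8 (assumed sizes), four arms, N = 120 and no treatment effect.

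- Adding smoking cut the model SE by 0.5-2.6% at d = 0.5 and 2.2-9.2% at d = 1 as p went from 5% to 30%. The formula, as 1 - 1/ratio, gives 0.6-2.5% and 2.3-9.1%.
- At p = 0.30, d = 1, the ratio of model SE to the observed spread of estimates was 1.11 without smoking (formula 1.10). This ratio is noisier: its Monte Carlo error is about 1/√(2 × 3000) = 1.3%, and single settings differ from the formula by up to 3.4 percentage points. For small d the formula is the better guide.
- In that setting, rejection at nominal 0.05 was 0.030 for a main effect and 0.024 for the four-group F test without smoking. With smoking it was 0.049 and 0.046.
- At N = 70, p = 0.30, d = 1, the cut in SE was 9.4%, much as at N = 120.

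**Residual SD for the definitive trial.** The SD is overstated by the same percentages. Required sample size scales with its square, so it rises by p(1-p)d²: 1.2-5.3% at d = 0.5 and 4.8-21% at d = 1.

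**Repeated-measures model.** The group-by-time test uses within-subject error. With complete data, a smoking term that is constant over time is absorbed by the differences between women, so adding it leaves that test unchanged. Only a smoking-by-time term can change it. The simulation did not cover this model, and the percentages above do not apply to it.

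**The case against.** - **Smoking may not be prognostic given baseline.** The article never says why it stratifies by smoking, and its Background does not link smoking to the outcomes. A reader might infer that the sponsor expected smoking to matter; the text does not say so. This stands: the effect is conditional and can be zero.
- **The larger figures need generous assumptions.** One full residual SD beyond the baseline value is a strong effect, and 10% needs it together with 30% smokers. This stands.
- **Balance may be imperfect.** At 5% prevalence there would be 6 smokers among 120 women across four arms, so incomplete blocks and dropout could leave that stratum uneven. This stands, and the gain there is small anyway.
- **The SD is imprecise regardless.** Its relative sampling error is about 1/√(2 df): 6.6% at N = 120 (115 df) and 8.8% at N = 70 (65 df). An overstatement of 0-3% lies well inside that and makes the definitive trial slightly larger, not underpowered.
- **The primary outcomes are untouched.** Feasibility, recruitment, adherence and attrition do not depend on these models. This stands.
- **An unseen analysis plan may add smoking.** It may, but the article names its adjustment set and model factors, and smoking is absent from both. The mismatch is in the published text, so this does not remove the point.

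**Conclusion.** The point holds as a minor one. The stated models omit the only factor that the randomisation is stratified by. Where smoking predicts an outcome beyond its baseline value, the ANCOVA standard errors are too wide: by about 0.6-2.6% at 0.5 residual SD and about 2-10% at 1 SD, for an assumed prevalence of 5-30%. With no such effect the overstatement is nil. Both prevalence and effect are assumptions.

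A reader might infer that ignoring the stratification biases the treatment estimate or raises the false-positive rate. It does neither: balance on smoking keeps the estimate unbiased, and the test errs towards caution. Nor can one say outright that the standard errors will be too wide, because the article does not show that smoking is prognostic given baseline.

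**What to change.** Add current smoking (yes/no, as recorded for randomisation) to the ANCOVA alongside the baseline value. Report the residual SD from that model for sizing the definitive trial. Later questionnaire answers on smoking should not replace the randomisation value.

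In the repeated-measures model, include smoking and smoking-by-time; the main effect alone does not alter the group-by-time test.

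The ANCOVA change costs one degree of freedom. With two smoking categories and three time points, the repeated-measures change costs one between-subject degree of freedom and (2 - 1) × (3 - 1) = 2 within-subject degrees of freedom. No new data are needed, since smoking is already recorded at baseline and used at allocation. If smokers are few, little is gained and little is lost.

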### Interventions

Participants were advised to take two servings of a powdered vitamin D and calcium plus semi-skimmed milk daily during breakfast and afternoon snack or supper to avoid concomitant intake of the prenatal iron supplements routinely prescribed for consumption with hot main meals (e.g. lunch or dinner). Twenty grams (20 g) of powdered semi-skimmed milk (of a commercial brand available in Brazil) is mixed with a sachet (2 g), containing calcium (CAPOLAC 500 mg) [48] and vitamin D_3_ (500 IU), to be reconstituted in 200 mL of potable water for each serving or other preparations (i.e. to consume with kneaded fruits, fruit smoothies, yogurt, porridge, etc.). Sachets with vitamin D/calcium and milk powder were provided monthly to participants in the fortified group during routine prenatal visits.

In the first dental session, a full periodontal examination was repeated to allow comparison with the first examination done during recruitment (screening) and check the agreement between the two dentists. After that, conventional non-surgical PT, consisting of prophylactic dental polishing to remove the sticky bacterial film that forms on the teeth overtime, scaling and root planning, as necessary, was undertaken throughout pregnancy, up to delivery (Fig. 1). The periodontal treatment is carried out at the Municipal Health Centre of Duque de Caxias. The treatment is performed by a qualified and trained dentist who was not involved in the screening procedure and was blind regarding group allocation.

PT started right after the randomisation to ensure early therapy initiation for the relevant treatment arms. The number of treatment sessions depended on the severity of the disease. However, participants were allowed up to five treatment sessions. In each session, participants also received personalised oral hygiene instructions. Standard fluoride toothpaste, without any additional component that could interfere in results, a toothbrush and dental floss were provided to all participants. Monitoring sessions (reassessment of dental conditions) were taken at 2-month interval. If necessary, PT and oral hygiene instructions were repeated.

All participants were advised not to alter their routine physical activity throughout the study and not to consume any supplements other than the ones provided by the clinics. Throughout pregnancy, participants were allowed to consume 400 μg/d folic acid and 60 mg/d ferrous sulphate, as provided during standard prenatal care in Brazil.

### Control group

The control group are the women assigned to the semi-skimmed powdered milk with non-fortified sachet (placebo) with similar colour, flavour, smell and texture as well as before and after dilution than fortified sachet, during pregnancy and late onset PT (after delivery). Late-onset PT starts after postpartum assessment, as part of the routine dental care in the prenatal clinic. This strategy is considered a more acceptable approach in comparison to offering no PT intervention, since the possibility of being assigned to an ‘untreated’ group could limit recruitment and is more ethical.

All participants were informed about the benefits of dairy food intake during pregnancy and given a brochure to take home with general information about healthy diet and oral health hygiene instructions once they entered the study.

### Dental examination

After initial screening, participants underwent a full periodontal examination at baseline (T0) and postpartum (T2). Periodontal examination was performed in full mouth at six sites per tooth (known as mesiobuccal, mid-buccal, distobuccal, mesiolingual, mid-lingual and distolingual), using North Carolina periodontal probes, dental mirror and gauze, but without X-rays. The model chosen is justified because no partial record model presents reliability to replace full mouth examination [49]. The T0 and T2 evaluations take place in the recruitment room, using a simple chair and a forehead flashlight. Maintenance examinations are performed to assess the periodontal status of those who had finished the treatment during pregnancy, and these examinations are done every 2 months. Data collection included gingival bleeding on probing, probing depth, cementoenamel junction-gingival margin distance (CAL) and dental mobility. A tailored form was developed to register the data. Oral examination and treatment procedures were performed by calibrated and trained dentists. The dentists always calibrated their probing force using a scale right before the clinical examination. The recommended probing force was approximately 20 g of pressure [50].

### Process evaluation of qualitative data

Focus group discussions were held prior to trial recruitment to discuss issues regarding recruitment strategy, study design and data collection. In addition, group discussions were held throughout the study (second and third trimester) to assess potential barriers and facilitators to the intervention and data collection.

The process evaluation included qualitative data from focus group and interviews [51, 52].

To perform a content analysis [53], the specific process evaluation frame was developed including two major categories: (1) dietetics abilities to understand the way the women organise daily use of milk sachet with their habitual food and (2) health care and identification of their existing social support network in health care. The evaluation frame was used to generate content associated with two major categories. Six themes were derived from two categories: (1) how to make and consume the food; sharing of the food with other family members; and (2) intolerances social support network and challenges in social life, access to health unit and identification of events related to pain and discomfort. All researchers were trained to fill into a frame of content previously structured with data related to pregnant women’s speeches associated to the six themes described above. Initially, one pilot focus group was performed with five women of similar socioeconomic conditions to those attending the health clinic where the present study is taking place. After some adjustments in the content of questions, the data was coded into themes and classified into three levels to identify favourable factors and health events: favourable, not favourable and neutral.

Second focus group regarding the culinary knowledge, health care practices including oral health and network social support at Duque de Caxias territory was performed prior to recruitment with 13 pregnant women attending the health centre. Thus, in the present study, we evaluated some of the barriers and enablers to participation, recruitment and intervention delivery, as well as the difficulties to go to the health unit.

Group discussions were held during the study after recruitment to assess potential barriers and facilitators to the intervention delivery and data collection. These group discussions provided qualitative data about potential acceptability. Additionally, monthly individual meetings were organised in the health centre with participants throughout the study to complement and update the qualitative data collection. Sentences and phases were registered and added into the frame, and frequency of occurrences, the patterns and the sequence of data are analysed. These data were then used to assist follow-up management and improve compliance with the intervention (e.g. suggestions on how to overcome reported barriers regarding milk consumption or monotonous diet). At the end of each participant’s involvement in the study, they were asked to complete an anonymous evaluation questionnaire to gain insights about women’s participation experience, acceptability and compliance to the study protocol.

### Adherence

Adherence were routinely assessed counting the unused sachets monthly, i.e. number of returned sachet by pregnant women in their monthly visit. SMS reminders to consume the sachets and milk were sent (once a week) to participants to help prevent attrition. A surplus of plain milk powder was provided to all women with young children to ensure dose fidelity. Acceptance of the intervention was evaluated via a questionnaire comprising questions about quality of taste (both milk powder with fortified and placebo sachet), possible difference in taste between those provided by the study and the commercial ones that they had tried. The amount of sachet consumed and suggested time of consumption, as well as the continuation of the program were evaluated.

Moreover, in the focus group, the issues raised regarding barriers to comply with the intervention protocol were addressed (e.g. new recipes are provided to women who complain about monotonous diet; possibility of home delivery of the powdered milk and sachet, etc.).

A social media group in a free mobile app was created to promote participant engagement and peer interaction. This strategy may reduce the attrition rate and improve the commitment with the project.

